#### Contents of the health coaching program

Overall, the health coaching sessions will focus on utilising principles of behaviour change and self-regulation to assist participants with:
Increasing physical activity: Health coaches will assist participants to develop a tailored physical activity plan suitable to their individual lifestyle preferences;Decreasing sedentary behaviour: Participants will be encouraged to increase daily incidental physical activity and decrease sitting time;Achieving their health-related goals: The health coach will provide ongoing support and motivation to help participants achieve their personal physical activity and health-related goals. Health coaches will continually review participant progress with achieving their goals and assist with adjusting goals if necessary or as desired by the participant.

The contents of the *Standard Coaching* module will be individually tailored to meet the needs for people with chronic LBP. The tailored content will be informed by evidence-based recommendations for managing chronic LBP (see Table 3).

**Table 3 Tab3:** Tailored health coaching content for chronic LBP

**Tailored health coaching content for chronic LBP**	
Goal-setting:	
• Mutually establish a physical activity goal with the participant at commencement of the health coaching program. Where relevant, this will include ongoing adherence to the exercise program prescribed by their hospital physiotherapist prior to discharge from treatment.	
• Establish other health-related goals that are meaningful to the participant (i.e., reducing weight, achieving a healthy diet, reducing alcohol consumption).	
Promotion of exercise and physical activity:	
• Explore barriers to exercise and physical activity participation (e.g., time, access, financial resources, social comfort).	
• Promote participant-led problem-solving skills to encourage overcoming perceived and real barriers to exercise or physical activity participation.	
Support:	
• Empower patients to foster self-efficacy and take charge of their own health, including monitoring their own symptoms and capacity to adhere to goals.	
• Encourage involvement of family members, partners, or friends for social support with achieving goals.	
• Provide continual motivation, encouragement, and support for the use of positive self-management strategies (e.g., physical activity, exercise).	
Interpersonal skills:	
• Build report, trust, and commonality with the participant.	
• Directly involve the participant in the problem-solving and decision-making processes.	
• *Educate and advise participants that the presence of pain does not always equal to harm.*	
Education:	
• *Educate and advise participants that many findings on imaging are common and do not necessarily identify the exact cause of pain. Further, imaging should only be carried out when consideration of serious pathology is clinically indicated.*	
• Identify and address unhelpful beliefs about their condition or progress.	
• *Educate and advise participants on the benefits of exercise and the consequences of inactivity such as prolonged bed rest (*i.e.*, muscle weakness).*	
• *Assist participants in navigating decision-making processes surrounding whether additional care from hospital, medical, or health services for LBP is necessary.*	
Pacing and activity modification:	
• *Encourage participants to maintain engagement in usual activities (*e.g.*, occupational, leisure).*	
• *Promote activity modification when required (*i.e.*, regress the difficulty of an exercise or activity, perform alternative exercises or tasks that do not elicit painful symptoms, minimise sustained repetitive postures and activities, minimise excessive loads when sitting, bending, or twisting).*	
• Educate and advise participants on incidental opportunities to increase physical activity levels when exercise may not be feasible (e.g., use public transportation, walk to the shops, stand at work, spend less time sitting at home).	
• *Encourage activity pacing when required, according to the participant’s physical capacity and goals.*	
Identifying and addressing psychological factors:	
• *Screen and address common psychological factors in chronic LBP populations (*e.g.*, fear avoidance, catastrophising, familial and social stress, work pressures, financial pressures).*	
• De-escalate potential perceived threats.	
• Ask simple and unambiguous questions.	
• *Avoid using catastrophising terms when discussing pain (*e.g.*, bulging disc, crumbling discs, degenerated discs).*	
• Use positive, supportive, and empathetic language.	
Reframing:	
• Focus problem-solving on the participant’s functional ability (i.e., improved ability to complete certain tasks or activities), instead of drawing attention to their pain.	
• Focus on activities that the participant can perform and what they are willing to try.	
• *Encourage participants to continue safe participation in exercise, even in the presence of acute symptoms (*i.e.*, flare-ups of LBP).*	
• Focus on activities that the participant has been able to perform successfully and provide ongoing encouragement for future success.	

Items in italics indicate content which has been tailored specifically for chronic LBP

After completing the *Standard Coaching* module, participants will be given the option to discontinue the program (i.e., graduation), re-enrol for further health coaching sessions, or opt into a free SMS maintenance support program *(Get Healthy Stay Healthy)* for an additional 6 months. The option selected by the participant will be recorded. For participants who opt into the *Get Healthy Stay Healthy* maintenance support program, they will receive automated, standardised (pre-scripted) motivational SMS reminders tailored towards 3 distinct goal categories: (1) physical activity, (2) diet, (3) weight maintenance. Participants will be asked to select one-to-two goal categories of interest and indicate their preferences for the SMS reminders (i.e., frequency of receiving reminders, number of reminders received per goal category). Their personal health coach will establish specific behaviour goals (e.g., walk for 30 min daily), personal barriers (e.g., distracted and often miss walking time), and enablers (e.g., set phone alarm for 6 pm daily), which will be embedded into the SMS messages. At 3 months into the *Get Healthy Stay Healthy* program, the health coach will phone the participant to monitor their progress and adjust the goal/s or reminder preferences as needed. At 6 months, the health coach will phone the participant to confirm completion from the SMS program (i.e., graduation) and encourage ongoing self-maintenance of positive health behaviours.

### Training

A series of training workshops will be implemented. Physiotherapists from the outpatient musculoskeletal physiotherapy departments of participating hospital sites will receive training from the research team to upskill on the process of identification of interested patients to the research team. The research team will undergo training to upskill on recruitment procedures (i.e., consent, eligibility screening). The designated investigator responsible for coordinating referral of participants to the Get Healthy Service® at each hospital site will receive training for managing the process (i.e., use of the digital referral form, provision of evidence of medical clearance). Health coaches delivering the study intervention will undergo a training workshop to familiarise themselves with the health coaching content which has been tailored to match the needs of chronic LBP (see Table 3). Health coaches will also receive training regarding indicators and procedures for clinical escalation (see Additional file 9).

### Assessment of intervention fidelity and engagement

#### Fidelity of the referral process

We will assess fidelity of the referral process by recording the total number of participants who are randomised to the support system and successfully enrolled into the Get Healthy Service® (i.e., completion of registration call) and expressing this as a percentage of the total number of participants are randomised to the support system group.

#### Fidelity of the health coaching program

The Get Healthy Service® conducts internal health coaching call audits for 1% of all calls per month carried out by the service. The audits are based on the following key criteria: security and privacy, clinical best practice, health coaching (i.e., effective utilisation of health coaching skills and techniques), call etiquette, documentation. Further, in the initial period of study implementation, the Get Healthy Service® will perform targeted auditing of health coaching calls delivered for participants specifically referred from the trial. The purpose will be to ensure that appropriate clinical best practice and high quality referral processing are achieved.

The research team will assess fidelity of the health coaching program by evaluating the following: (i) number of participants randomised to the support system who successfully establish a physical activity goal at commencement of the health coaching program; (ii) total number of health coaching sessions received per participant; (iii) number of participants who complete the Get Healthy Service® *Standard Coaching* module, where completion will be defined as receiving the 10 allocated health coaching sessions or achievement of participant goals. Data will be collected by the Get Healthy Service® and provided to the research team.

#### Participant engagement

We will assess participant engagement with the study intervention by recording the total number of participants who successfully complete the *Standard Coaching* module and expressing this as a proportion of the total number of participants who are successfully enrolled into the *Standard Coaching* module (tailored for chronic LBP).

### Monitoring adverse events

The research team has designed this study to minimise or prevent potential risks. Expected adverse events include: i) flare-ups of LBP, ii) muscle soreness, swelling, or muscle cramps related to commencement of unaccustomed exercise; iii) unexpected trip/fall. During the intervention period, participants will complete a paper-based weekly diary to capture any adverse events which may occur during the 6-month intervention period (see Additional file 8). Participants will be required to document any adverse events by answering the question: ‘Did you experience any of the following this week?’. Possible responses will include increased back pain, pain elsewhere, muscle soreness, swelling, muscle cramp, trip/fall, emotional distress, serious event, and other symptoms. If relevant, participants will be asked whether the event persisted more than 24 h (yes or no) and whether medical attention was sought (yes or no). If the participant perceives that the adverse event is directly related to participation in the study or they have ongoing unresolved concerns about the event, the diary contains written instructions directing them to contact the research team as soon as possible. The research team will monitor the adverse event until resolution. If participants are harmed from taking part in the study, there will be no special compensation arrangements.

### Follow-up data collection

At 6 and 12-months from baseline assessment, participants will complete a follow-up online (electronic) questionnaire to record the study outcomes (see Additional file 4). At each timepoint, participants will receive the link to complete the respective online questionnaire via SMS or email, depending on their preference. At the 6-month follow-up, the participant will also repeat the procedure of wearing the accelerometer device and completing the physical activity logbook for 7 consecutive days. Participants will receive the accelerometer, an instruction sheet for self-mounting the device, the logbook, and a pre-paid reply envelope via post.

All participants will complete a brief questionnaire every fortnight during the 12-month assessment period (see Additional file 5). Participants will receive a link to complete the online fortnightly questionnaire via SMS or email. The questionnaire will collect self-reported data related the primary outcome (i.e., use of hospital, medical, and health services for LBP), and select secondary outcomes (i.e., pain intensity, self-management behaviours). Participants will be asked whether they experienced LBP (yes or no) and whether they sought any care or treatment for LBP (yes or no), in the past fortnight. Where relevant, follow-up questions will be asked regarding the mean pain intensity and number of days experiencing LBP, the type of care or treatment sought, and any costs or travel time associated with managing their LBP.

In addition, an unblinded member of the research team will briefly contact all participants at 3, 6 and 9 months to identify any concerns of the participant regarding participation in the study, such as potential barriers towards ongoing engagement with responding to fortnightly and follow-up questionnaires. The research team will use this information to develop strategies to promote ongoing study engagement (e.g., explain to participants the importance of obtaining a complete data set for the study). To maintain engagement with participants in the usual care group, participants in the usual care group will be offered the opportunity to enrol into any of Get Healthy Service’s® programs at the completion of their 12-month follow-up assessment.

### Monitoring contamination

The Get Healthy Service® is well-established and free to use for state residents. It is possible that participants in the usual care group may self-refer to the Get Healthy Service® and enrol in any of the health coaching programs offered. To minimise the risk of contamination, participants will be informed prior to study enrolment that those randomised to the usual care group will be asked to not participate in the health coaching intervention. Participants will also be informed that at the end of their participation in the trial (i.e., after completing their 12-month follow-up assessment), they will be offered the opportunity to enrol into the Get Healthy Service® and any of its programs. During the trial, participants will still be allowed to seek other forms of care or continue with the standard usual care provided to them by their physiotherapist at discharge from treatment.

If a participant in the usual care group self-enrols into any of the Get Healthy Service's® programs during the study period, we will not ask them to discontinue the program and will continue collecting data from them unless they choose to withdraw from the study entirely. At the conclusion of the study (i.e., after completion of the 12-month follow-up), a research team member will phone all participants in the usual care group to confirm whether they self-referred to any of the Get Healthy Service® programs during the intervention period. During this phone call, participants who express subsequent interest in the Get Healthy Service® will be offered enrolment into the service.

### Embedded qualitative study

We will conduct an embedded qualitative study of a sample of key stakeholders (including clinicians, trial participants, and health coaches and agents from the Get Healthy Service®) involved in the study. The purpose will be to identify factors related to the intervention, context, and individual, to inform the development of an implementation plan for scalability of the approach across New South Wales local health districts.

We will conduct a series of in-depth interviews and one or more focus groups to identify factors and processes that contributed to the program outcomes. The interviews and focus group(s) will be informed by the Consolidated Framework for Implementation Research (CFIR) [43], and will focus on exploring the following CFIR constructs: (1) intervention characteristics (e.g., relative advantage, adaptability, cost); (2) outer setting (e.g., patient needs and resources, external policies and incentives); (3) inner setting (e.g., implementation climate, relative priority, available resources); (4) characteristics of individuals (e.g., knowledge and beliefs about the intervention, individual identification with organisation); (5) processes (e.g., executing, engaging, reflecting and evaluating).

Participants will be purposively selected to ensure a range of demographics, health services, and experiences are captured, and interviews will continue until theme saturation is reached. We expect to conduct in-depth interviews with approximately 30 clinicians and trial participants, and a focus group involving health coaches and agents from the Get Healthy Service®. A mixture of inductive and deductive (drawing on the CFIR) interview analysis will be undertaken. Key themes will be used to guide development of recommendations for scalability of the support system.

### Data integrity and monitoring

A Data Monitoring Committee (DMC) will be convened to overview data collection and integrity. The DMC will approve the statistical analysis plan and research protocol. Interim analyses of baseline data may be undertaken, under the guidance and approval from the DMC. The integrity of trial data will be monitored by regularly scrutinising data sheets for omissions and errors. Data inconsistencies will be explored and resolved. The lead investigator will be responsible for overseeing trial safety and ensuring that the best interests of participants are observed at all times. The lead investigator will be blinded to allocation, unless unblinding is deemed essential to ensure participant safety. Adverse events will be reported to the reviewing Human Research Ethics Committee and study Sponsor in accordance with approved requirements. All data collected will be restricted to the lead investigator and select members of the research team.

### Protocol amendments

Any modifications to the protocol will be submitted to the reviewing Human Research Ethics Committee and acknowledged by the trial sponsor before implementation. Amendments will be communicated to the relevant trial registries and included in publications of trial results.

### Sample size calculation

The sample size is that required to detect a clinically meaningful between-group difference in the primary outcome, i.e., the total number of encounters with hospital, medical, and health services for LBP [44]. A total of 374 participants (*n* = 187 per group) will be recruited. The study will have 90% power to detect as significant, at the 5% level, a 30% difference in the rate of using hospital, medical, and health services for LBP between groups (i.e., an Incidence Rate Ratio of 0.70 using negative binomial regression analysis) over the 12-month study period. The 30% difference in the rate of using hospital, medical, and health services for LBP is based on our research of patients’ perceptions of a clinical worthwhile effect of interventions for LBP [45]. Estimates were based on a base rate exposure (β0) of 0.2 [total of 2 care-seeking events in the usual care group per fortnight (data from pilot)], assuming a correlation of 0.3 (R^2^ = 0.09) between covariates and predictor (treatment), using negative binomial regression model (G*Power® software) [46]. Estimates allow for a loss to follow-up of 10%.

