### Randomisation

After baseline assessment has been completed and the participant has been discharged from treatment, participants will be randomised with 1:1 allocation ratio to either the support system or usual care group. Treatment allocation will be performed using a computer-generated random allocation schedule operated by a remote unblinded researcher to ensure concealment. As participants will be randomised after discharge from treatment, with minimal potential for treatment contamination, randomisation will be at participant level. Randomisation will be by random permuted blocks of 4 and 6. Participants will be notified of their allocation via phone call from an unblinded research assistant. Select members of the research team will be unblinded to treatment allocation (i.e., main trial co-ordinator, the designated investigator managing referrals to the Get Healthy Service®, unblinded statistician monitoring trial safety, health coaches and agents from the Get Healthy Service®). Otherwise, all other research team members will remain blinded to treatment allocation. Participants will not be blinded to group allocation.

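### The sample size calculation assumes R² = 0.09 between covariates and randomised treatment; the expected value is 0, and the term, if applied, inflates the required number by about 10%

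*Protocol article*

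**What the plan says.** Protocol article, Sample size calculation: "A total of 374 participants (*n* = 187 per group) will be recruited". The section goes on: "The study will have 90% power to detect as significant, at the 5% level", for "an Incidence Rate Ratio of 0.70 using negative binomial regression analysis", over 12 months and allowing for 10% loss to follow-up. Among the inputs it lists a correlation of 0.3 (R² = 0.09) "between covariates and predictor (treatment), using negative binomial regression model". The authors themselves put treatment in brackets as the predictor, so there is no doubt which relation the sentence describes.

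Protocol article, Randomisation: once baseline assessment is complete, "participants will be randomised with 1:1 allocation ratio to either the support system or usual care group". Allocation is at participant level, in random permuted blocks of 4 and 6.

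Protocol article, Statistical analysis: the negative binomial model adjusts for six characteristics, namely baseline pain, baseline disability, previous treatments, duration of symptoms, co-morbidity and age. As described, all six precede allocation.

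**The concern.** An R² between the predictor of interest and the other covariates is a collinearity penalty. It belongs in the planning of an observational study, where exposure and confounders are correlated and part of the information on exposure is lost on adjustment. In a trial with individual randomisation, covariates fixed before allocation have zero population correlation with treatment, so there is no such loss to plan for beyond chance imbalance.

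At stake is the accuracy of the published justification for recruiting 374 people. If the term was used, the stated power is slightly too low for that number. The section also presents adjustment for prognostic covariates as a cost, when in a randomised trial its usual effect is to reduce residual variation. Another team reusing the calculation would carry the same penalty into another randomised design.

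**Working it through.** **Inputs.** From Sample size calculation: N = 374, power 90%, 5% level, rate ratio 0.70, R² = 0.09, loss 10%, base rate 0.2. From Statistical analysis: six covariates. Assumptions: two-sided test (the side is not stated), each covariate enters as one term, and R² enters in the usual way, as a factor 1/(1 − R²) on the required number.

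**1. Can 374 be reproduced?** The Wald formula for two equal groups is

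N = 2(z_α + z_β)² [1/μ0 + 1/(0.7 μ0) + 2k] / (ln 0.7)² / (1 − R²),

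where μ0 is the mean count in the usual care group and k is the dispersion. With z_α + z_β = 1.960 + 1.2816 = 3.2415, R² = 0.09, division by 0.9 for loss, and k = 0 (Poisson):

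| Reading of the base rate | μ0 | Recruited N |
|---|---|---|
| 0.2, one period | 0.2 | 2,449 |
| 2, one period | 2 | 245 |
| 0.2 per fortnight, 26 fortnights | 5.2 | 94 |
| 2 per fortnight, 26 fortnights | 52 | 9 |

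Two other Poisson formulas (Signorini, and Wald with the null variance corrected) give 2,183 and 2,403, 218 and 240, 84 and 92, and 8 and 9 for the same four rows. One-sided testing does not produce 374 for these readings either. The negative binomial form reaches it only by solving for a dispersion that the article does not state. For example, k = 0.694 at μ0 = 5.2 gives 336.7 evaluable, and 336.7/0.9 = 374; k = 0.32 at μ0 = 2 gives 336.6 evaluable. So 374 is not reproduced.

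**2. The ratio, which needs none of the missing inputs.** Whatever μ0 and k are, N is proportional to 1/(1 − R²). Relative to R² = 0, the stated input multiplies N by 1/0.91 = 1.099. Check: the two negative binomial examples above fall from 336.7 and 336.6 evaluable to 306.4 and 306.3 when R² is set to 0.

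**3. What R² does randomisation give?** With p covariate terms and n analysed, the chance R² has mean p/(n − 1).
- n = 337 (374 × 0.9 = 336.6), p = 6: 6/336 = 0.018.
- n = 374, p = 6: 6/373 = 0.016.
- The approximate distribution for n = 337 is Beta(3, 165): 95th percentile 0.037, and probability of reaching 0.09 about 2 in 100,000.
- For the mean to be 0.09, the model would need about 0.09 × 336 = 30 terms.

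**4. Consequence, if 374 was computed at exactly 90% power with the term included.**
- N for 90% power = 374 × 0.91/(1 − R²). R² = 0 gives 340.3, and R² = 0.018 gives 346.6. Rounding the evaluable number up before allowing for loss gives 307/0.9, or 342, at R² = 0.
- Power at 374 = Φ(3.2415 × √[(1 − R²)/0.91] − 1.960). R² = 0 gives Φ(1.438) = 0.925, and R² = 0.018 gives Φ(1.407) = 0.920.
- With a one-sided 5% test and R² = 0: Φ(2.926/√0.91 − 1.645) = 0.923, so the side of the test hardly matters.

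**The case against.** The strongest reply is that nothing depends on this. If the term is in the 374, the trial is a little larger than it had to be and its power is at least the stated 90%. The analysis, the estimand and the reading of the result are untouched, and about two points of extra power lies within ordinary planning margin. That stands, and it caps the importance of the point.

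A second reply is that no corrected number has been proved. That also stands. The article gives neither dispersion nor mean exposure, which a condensed article may leave to the full protocol. The base rate of 0.2 is explained as a total of 2 events per fortnight in the usual care group. That may be a group total behind a per-person rate, but the pilot group size needed to check it is not shown. The arithmetic around 374 is ambiguous too: 340 × 1.1 = 374 exactly (a loss allowance), while 340/0.91 = 373.6 also rounds to 374 (the R² term). A reader might therefore infer that 374 and 90% contradict the other stated inputs. The document does not support that, because those inputs alone imply no particular number.

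A third reply is that 0.09 might be a cautious allowance for chance imbalance, or a correlation between covariates and outcome. Neither rescues it. It is five times the expected chance value and well beyond the 95th percentile, and allowing for more than six terms would not close that gap at any plausible model size. A covariate–outcome correlation would lower the required number, so the sentence would misname the quantity and the inflation would have the wrong sign.

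**Conclusion.** The point holds as a minor one. As written, R² = 0.09 between covariates and treatment is an unjustified planning input under individual 1:1 randomisation. The expected value is 0, or about 0.018 by chance with six single-term covariates. The inflation factor of 1.099 is firm, provided the term was applied in the usual way. The figures of about 92% power at 374, or about 340 to 347 participants for 90%, hold only if 374 was computed at 90% power with the term included and all other inputs held.

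Two stronger readings go too far. The trial is not shown to be underpowered by this input; any error is in the conservative direction. Nor does randomisation make a non-zero sample R² impossible. It makes the expected value zero and a value as large as 0.09 extremely unlikely.

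**What to change.** Rerun the original calculation with R² between treatment and covariates set to 0, or to about 0.02 to allow for chance imbalance. Keep 374 and take the restated power from that rerun, not from the conditional figures above. Beside it, state the dispersion, the exposure period and the base rate used (with its unit), so that the number can be checked. If a correlation between covariates and outcome was intended, correct the description, and credit the covariates, if at all, as a reduction in residual variation and not as an inflation. The cost is one rerun and a few reworded sentences. Recruitment, conduct and analysis do not change.
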